### Statistical analysis

For clinical data, statistical analyses will be analyzed using Statistical Package for the Social Sciences (version 19.0). Two-sided tests will be considered statistically significant if *P* ≤ 0.05. Cases of any missing data should be listed and the reasons should be indicated. The main efficacy analyses will be conducted based on the intention-to-treat principle. Sociodemographic information and outcome indicator will be presented with the mean ± standard deviation or the frequency (%) for the real mPFC-rTMS group and the sham mPFC-rTMS group. Independent *t* tests will be used to compare the outcome indicators between the two groups before and after mPFC-rTMS. Paired *t* tests will be used to compare the pre-rTMS and post-rTMS outcome indicators within each group. A repeated measures analysis of variance with adjustments for non-sphericity will be applied to analyze the group differences and time-dependent effects of rTMS on outcome indicators.

For fMRI data, statistical analyses will use SPM12 (http://www.fil.ion.ucl.ac.uk/spm), Data Processing & Analysis of Brain Imaging toolbox (http://rfmri.org/dpabi), and VBM8 toolbox (http://dbm.neuro.unijena.de/vbm) plugged into MATLAB_R2018a (Mathworks, Inc., Natick, MA, USA). Original data will be preprocessed: slice timing, affine head motion, nonbrain extraction, spatial smoothing, and temporal filtering will be applied. The regional resting-state fMRI time series will extract for the bilateral mPFC by using the average functional time series of all voxels within each region. Significance was set at a *P* value < 0.05 after correcting for multiple comparisons using false discovery rate (FDR) correction. Pearson correlation will be used to investigate the RSFC between bilateral mPFC and the whole-brain regions, and then a Fisher’s *r*-to-*z* transform is employed. mPFC-based functional connectivity pre-rTMS and post-rTMS between the real and sham mPFC-rTMS group will be compared using independent *t* tests. Paired *t* tests will be used to compare pre-rTMS and post-rTMS mPFC-seed functional connectivity within each group.

There will be no interim analysis.

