### Sample size

This study aims to determine the efficacy and brain mechanism of mPFC-rTMS in ID patients. Based on preliminary experiments, the PSQI score significantly decreased by 4.43 ± 3.60 in the group treated with mPFC-rTMS compared to 1.30 ± 2.58 in the control group. Based on a power analysis, 26 patients per group were required to detect a significant difference (power = 0.9, *α* = 0.05, two-sided). Thus, considering a 15% dropout rate, we plan to recruit 30 patients per group to compensate. As to fMRI research, there is no known sample size calculation. However, for the exploratory study, 15 to 30 patients are adequate to test the null hypothesis [26].

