### Outcome

#### Primary outcome

Our primary outcome will be the mean change scores of insomnia severity assessed using PSQI from baseline to the end of the treatment period. The PSQI is a 19-item insomnia assessment tool consisting of seven component scores, including sleep quality, sleep latency, sleep duration, sleep efficiency, sleep disorders, hypnotic medication, and daytime dysfunction. The higher score reflects the worse sleep quality.

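### None of the listed PSQI tests is named as primary, and none is stated to be the baseline-to-end-of-treatment contrast on which the trial is defined and sized

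*Protocol article*

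**What the plan says.** The Primary outcome section of the protocol article fixes one endpoint at one time: "Our primary outcome will be the mean change scores of insomnia severity assessed using PSQI from baseline to the end of the treatment period".

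The Sample size section uses the same quantity. In preliminary work the PSQI "decreased by 4.43 ± 3.60 in the group treated with mPFC-rTMS compared to 1.30 ± 2.58 in the control group". From this it derives 26 per group at power 0.9 and two-sided α = 0.05, raised to 30 for 15% dropout. The Trial design section gives the aim as superiority of real over sham stimulation and sets three assessments: baseline, post-treatment, and 8 weeks after the last session.

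The Statistical analysis section lists three procedures for all clinical outcomes together, under one significance rule (P ≤ 0.05, two-sided):

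- Between arms, by the two-sample method: "tests will be used to compare the outcome indicators between the two groups before and after mPFC-rTMS". The wording covers baseline as well as the period after treatment.
- Inside each arm, a paired t comparison of scores at the two times.
- Across visits, with no term or time point singled out: "A repeated measures analysis of variance with adjustments for non-sphericity will be applied to analyze the group differences and time-dependent effects of rTMS".

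The only statement about the principal analysis concerns the population: "The main efficacy analyses will be conducted based on the intention-to-treat principle". It does not say which test that analysis uses.

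**The concern.** The outcome and the sample size point to one comparison: real versus sham, in PSQI change from baseline to end of treatment. The analysis section names several procedures, and none is stated to be that comparison.

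- The independent t test before treatment compares two randomised groups at baseline and says nothing about efficacy.
- The independent t test after treatment most naturally compares end-of-treatment scores.
- The paired tests do not compare the arms.
- The ANOVA offers a group effect and a group-by-time interaction, and neither term is singled out.

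Two things are at stake. With several candidate tests at 0.05 and none declared decisive, the trial's conclusion could rest on whichever is favourable. And if the post-treatment t test turns out to be the deciding one, its power is not the figure computed for change.

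**Working it through.** **Inputs from the Sample size section.** Changes of 4.43 (SD 3.60) and 1.30 (SD 2.58); 26 per group needed, 30 recruited, 15% dropout. The correlation between PSQI visits is not given, so I assume 0.3 to 0.7, with equal variances across visits.

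**The plan's own figure.** Difference = 4.43 − 1.30 = 3.13. Pooled SD = √((3.60² + 2.58²)/2) = 3.132. Required n per group = 2 × (1.960 + 1.282)² × (3.132/3.13)² ≈ 21.04, so 22, or 23 with the t distribution. The stated 26 is not reproduced, but it errs on the safe side: it has about 94% power by the t distribution. The point made here does not depend on that gap.

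**Outcome against tests.**

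| Listed procedure | What it compares | Is it the primary contrast? |
|---|---|---|
| Independent t, before | Arms at baseline | No |
| Independent t, after | Arms after treatment | Not stated to be on change |
| Paired t | Visits within one arm | No; the arms are not compared |
| ANOVA group effect | Arms averaged over visits | No; with baseline entered, it is averaged in |
| ANOVA group-by-time | Differential change | In part; with three visits entered it is a joint 2-degree-of-freedom test that includes follow-up |

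**False-positive chance with several candidate tests.** I simulated trials with no effect: three visits, normal data, equal correlation 0.3, 0.5 or 0.7, 25 or 30 per arm, 20,000 trials per setting.

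- Post-treatment t, ANOVA group effect or interaction significant at 0.05: about 11–12%, counting both directions.
- The same event with the end-of-treatment means favouring rTMS: about 6%. A single two-sided test at 0.05 gives 2.5% in that direction.
- Post-treatment t or interaction only, without the group effect: about 9%, both directions.
- All three plus a t test on change: about 13–14%, both directions.

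**Power at 25 per arm** (30 × 0.85 = 25.5, rounded down). I hold the SD of change at 3.132 and the effect at 3.13.

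- SD of a single score = 3.132/√(2(1 − ρ)).
- Residual SD after baseline adjustment = that SD × √(1 − ρ²).
- Power from the noncentral t distribution.

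| Assumed ρ | SD of a score | Post-only | Change | Baseline-adjusted |
|---|---|---|---|---|
| 0.3 | 2.65 | 98% | 93% | 99% |
| 0.4 | 2.86 | 97% | 93% | 98% |
| 0.5 | 3.13 | 93% | 93% | 98% |
| 0.6 | 3.50 | 87% | 93% | 97% |
| 0.7 | 4.04 | 76% | 93% | 96% |

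With all 30 per arm, post-only power is 92.6% at 0.6 and 83.9% at 0.7.

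**Paired test in the sham arm.** At the control figures and n = 30, t = 1.30/(2.58/√30) = 2.76, P = 0.01, and the power of that test is about 76%. A significant sham change is therefore likely, and it carries no information on superiority.

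**The case against.** **An analysis plan could name the primary test.** It could, and its absence here would be no finding if the protocol had left the tests open. But the protocol commits to specific tests, and they do not line up with its own outcome and sample-size basis. That mismatch stands in the text.

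**The plan does use baseline.** A reader might infer that it compares only raw scores and never examines change. The documents do not support this. The text says outcome indicators and never says raw, although a test before treatment does point to scores at each visit. The ANOVA has a group-by-time term that bears on differential change. What stands is that this term is not named as decisive and, with three visits entered, is not the end-of-treatment contrast.

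**Post-only is not simply underpowered.** At an assumed correlation below 0.5 it has more power than the change score, and at 0.5 the two are equal. Entry requires a PSQI above 11, which truncates baseline; this tends to lower the correlation and makes the equal-variance assumption doubtful. Only the dependence on an unstated correlation stands.

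**12% is not the rate of false claims for rTMS.** It counts both directions. In favour of rTMS it is about 6%, and it supposes that the ANOVA group effect would be accepted as success, which the protocol never says.

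**The paired tests are not presented as efficacy evidence.** That is correct. The hypothesis is real against sham, and the Introduction already acknowledges a sham response. Reporting them descriptively is a safeguard, not the correction of a claim.

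**Lack of baseline adjustment is not an error.** Agreed. An unadjusted comparison of change or of end-of-treatment scores is unbiased in a randomised trial. Adjustment gains precision only.

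**Conclusion.** The point holds in a limited form. The protocol fixes one primary outcome at one time and sizes the trial on it, then lists several tests at the same significance level without saying which decides, and without stating that any of them is that contrast.

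If three of these could each count as success, the two-sided false-positive chance is roughly double the nominal 5%, and the chance in favour of rTMS is roughly double 2.5%. These figures assume normal data, equal variances and equal correlations of 0.3–0.7 between visits.

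The power figures further assume the pilot difference and pooled SD of change. Under those assumptions the post-only test may do better or worse than the change score, while the baseline-adjusted analysis has the highest power throughout the range. The documents do not show that the analysis is biased, that the trial is too small, or that a within-arm result will be used to claim efficacy.

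**What to change.** State one primary analysis: the between-group difference in PSQI at end of treatment, from a linear model with group and baseline PSQI, with a 95% confidence interval and two-sided α = 0.05. With baseline in the model, the estimated group difference is the same whether the response is the end-of-treatment score or the change from baseline, so this matches the stated outcome.

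Then:

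- label the repeated-measures ANOVA and all other PSQI tests supportive;
- report within-arm changes as means with confidence intervals and no efficacy claim;
- drop the significance test at baseline and keep the descriptive table.

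The change should be made before unblinding. It costs a few sentences and one degree of freedom. Baseline PSQI is already collected, and no larger sample is needed.

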### Trial design

This study is designed as a prospective parallel-group, patient- and assessor-blinded, randomized controlled single-center clinical trial with two parallel groups to detect the superiority of real mPFC-rTMS over the sham mPFC-rTMS. Digital randomization table will be performed as block randomization with a 1:1 allocation assigned to either a real mPFC-rTMS group or a sham mPFC-rTMS group. The neuropsychological measurements, a 1-week sleep diary, a 1-day polysomnography (PSG), and fMRI scans will be performed at baseline, post-treatment (immediately after completion of the 20-day treatment), and 8 weeks follow-up (8 weeks after the last session). The detailed flowchart is shown in Fig. 1. The trial will be conducted in accordance with the SPIRIT reporting guidelines [25]. Ethical approval has been granted by the ethics committee of Zhenjiang mental health center (202007), and the trial is registered at ChiCTR (CHiCTR2100054154).

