#### Quality control and guarantee

At the begaining of the study, the whole research process, criteria for inclusion and exclusion, rTMS operation, curative effect observation, data collection and management, and adverse event reporting and recording will be trained for the researchers.

The trial will be withdrawn under the following conditions:Patients with deterioration conditionPatients with serious adverse events who need to stop rTMS treatmentOther serious physical diseases during the testFrom the medical and ethical perspective, the researcher considered that it is necessary to terminate the researchParticipants are reluctant to continue the study and withdrawal of informed consent for non-medical reasonsWithdrawal of informed consent

The research data will be recorded and stored correctly, completely, and consistent with the original data in the form of double data entry under the study management team which is set up to take charge of quality control and supervise the research process. The scale evaluation is completed by designated persons. PSG is conducted by professionals in the Sleep Rehabilitation Center of Zhenjiang Mental Health Center. fMRI is conducted by professionals in the Imaging Department of Zhenjiang Mental Health Center. When the subjects drop out, the researchers will interview by face to face, phone, or mail, and so forth to ask for reasons, record the time of the last treatment, and complete the evaluation items as far as possible. Patients with deterioration conditions, adverse events, and other serious physical diseases will be taken corresponding treatment measures. Patients who have been ranked with random numbers will be included in the statistical analysis if they received more than half of the treatment course. All dropouts will be analyzed according to the intention-to-treat principle after the trial.

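### No single primary analysis is named, and the three-visit repeated-measures ANOVA is a poor candidate: without imputation it is complete-case, and neither of its group tests is the end-of-treatment contrast

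*Protocol article*

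**What the plan says.** The Primary outcome section of the protocol article fixes one contrast: PSQI change between baseline and the end of treatment. Under Trial design, outcomes are measured at three visits: baseline, immediately post-treatment, and 8 weeks after the last session.

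The Statistical analysis section then lists three methods for the outcome indicators:

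- Independent t "tests will be used to compare the outcome indicators between the two groups before and after mPFC-rTMS".
- Within-arm paired t tests, before against after treatment.
- "A repeated measures analysis of variance with adjustments for non-sphericity will be applied to analyze the group differences and time-dependent effects of rTMS".

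None is named as primary, and no ANOVA term is named as the test of efficacy.

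On missing data and the analysis set, the same section says "The main efficacy analyses will be conducted based on the intention-to-treat principle" and "Cases of any missing data should be listed and the reasons should be indicated". The section on quality control adds "All dropouts will be analyzed according to the intention-to-treat principle after the trial". It also says that randomised patients "will be included in the statistical analysis if they received more than half of the treatment course". The Sample size section expects losses: "considering a 15% dropout rate, we plan to recruit 30 patients per group to compensate".

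**The concern.** A non-sphericity adjustment matters only with three or more time levels, so the ANOVA must span all three visits. Classical repeated-measures ANOVA uses only patients with every visit present. A patient who finishes treatment, gives an end-of-treatment PSQI and misses only the follow-up visit would therefore lose the primary-outcome observation. Without imputation, that cannot be squared with an intention-to-treat analysis of all dropouts.

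The target is also off. The ANOVA's group main effect is the between-arm difference averaged over three visits. One of these is baseline, where randomisation makes the expected difference zero. The interaction asks whether the arms differ in shape over time at all, which is a broader question than the primary contrast.

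Because nothing designates the deciding test, any of these results could be reported as the efficacy result, and their power differs widely.

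**Working it through.** **Inputs from the documents.** Pilot PSQI decreases are 4.43 (SD 3.60) and 1.30 (SD 2.58). The test is two-sided at 0.05, with 30 per arm and 15% dropout (Sample size, Statistical analysis).

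- Difference: 4.43 − 1.30 = 3.13.
- Pooled SD of change: √((3.60² + 2.58²)/2) = 3.13, so the standardised effect is 1.00.

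**The plan's own figure.** With these inputs, 90% power needs 22 per arm (normal approximation) or 23 (t), not the stated 26. The stated number errs on the safe side (power 0.94 at 26), and the mismatch does not bear on this point.

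**Patients at risk of exclusion.** 60 × 0.15 = 9, leaving 30 × 0.85 = 25.5 per arm. I use 25.

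**Assumptions, not in the documents.** Equal correlation ρ between visits of 0.3, 0.5 or 0.7. Share f of the end-of-treatment effect kept at follow-up of 1, 0.5 or 0. SD of change held at 3.13, so the SD at one visit is σ = 3.13/√(2(1 − ρ)) = 2.65, 3.13 or 4.04.

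**Group main effect.** Effect = (0 + 3.13 + 3.13f)/3 = 2.09, 1.57 or 1.04 points for f = 1, 0.5, 0. SD of the three-visit mean = σ√((1 + 2ρ)/3). At ρ = 0.5 this is 3.13 × √(2/3) = 2.56. With 25 per arm and f = 0, the noncentrality is 1.04/(2.56 × √(2/25)) = 1.44, which gives power 0.29.

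**Group-by-time interaction.** Noncentrality λ = (n/2) Σ(μ − mean)² / (σ²(1 − ρ)), where μ = (0, 3.13, 3.13f). Since σ²(1 − ρ) = 3.13²/2, ρ cancels. At n = 25, λ is about 16.7 for f = 1 or 0 and 12.5 for f = 0.5, on 2 and 96 degrees of freedom.

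**Tests at end of treatment.** Change-score t test: SD 3.13. Raw post-treatment t test: SD σ. Baseline-adjusted ANCOVA: SD σ√(1 − ρ²).

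Power at 25 per arm:

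| Test | ρ = 0.3 | ρ = 0.5 | ρ = 0.7 |
|---|---|---|---|
| ANOVA main effect, f = 1 | 0.96 | 0.81 | 0.52 |
| ANOVA main effect, f = 0.5 | 0.80 | 0.56 | 0.32 |
| ANOVA main effect, f = 0 | 0.46 | 0.29 | 0.17 |
| ANOVA interaction, f = 1 or 0 | 0.96 | 0.96 | 0.96 |
| ANOVA interaction, f = 0.5 | 0.89 | 0.89 | 0.89 |
| t test on change | 0.93 | 0.93 | 0.93 |
| t test on raw post-treatment score | 0.98 | 0.93 | 0.77 |
| Baseline-adjusted ANCOVA | 0.99 | 0.98 | 0.96 |

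**Illustration of selective loss.** This is a simulation of 20,000 trials with 30 per arm and no true effect. About 15% are missing at follow-up, and in the real arm only, poor responders are more likely to be missing (odds ratio 2.7 to 4.5 per SD). Deleting their end-of-treatment values biases the difference by 0.4 to 0.6 points and raises type I error to about 7% to 10%. Using all observed end-of-treatment values keeps it at 5%. The missingness pattern is assumed.

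**The case against.** A reader might infer that the plan has no valid test at the primary time point, or that it will discard about 9 patients. The documents support neither.

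- **The ANOVA is one of three methods.** The planned independent t test after treatment needs no follow-up visit, so it keeps the end-of-treatment PSQI of a patient who misses only that visit. This stands. What remains open is whether the t test decides the outcome, and whether it uses change or raw scores.
- **Dilution affects only the group main effect.** The wording on time-dependent effects can be read to include the group-by-time interaction, which keeps power of 0.89 to 0.96. This stands, and it rules out saying that the plan as a whole would miss a real benefit. The interaction is still not the primary contrast, and it suffers the same complete-case loss.
- **No text says that incomplete patients are dropped.** That follows from how the classical method works without imputation. An imputation rule may sit in an analysis plan not shown, and its absence here is no finding. The protocol also provides for completing dropouts' assessments as far as possible and encourages follow-up attendance. The point is that the named method and the stated principle cannot both hold unless something is added.
- **Nine is an upper bound.** The 15% is not tied to a visit. Patients who leave before end of treatment have no post-treatment PSQI to lose, and a mixed model gains no outcome information from them.
- **The bias figures rest on an assumed mechanism in one arm.** They show direction and rough size and are no forecast for this trial.

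The rule tying inclusion to the share of treatment received is more direct evidence against intention-to-treat than the ANOVA. It needs reconciling in its own right.

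**Conclusion.** The point holds in a limited form. The plan lists several between-group tests of PSQI and designates none as primary. Of these, the three-visit ANOVA fits worst. Without imputation it is complete-case, at a cost of at most about 9 of 60 patients, against a promise to analyse all dropouts. Its main effect carries 1.04 to 2.09 of the 3.13 points if between none and all of the benefit persists. Main-effect power at 25 per arm is 0.29 to 0.81 at a visit correlation of 0.5, and 0.17 to 0.96 over correlations of 0.3 to 0.7. Its interaction is adequately powered but answers an omnibus question.

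The right time point is within reach of the planned t test. The gain from a better primary analysis is therefore moderate: 0.96 to 0.99 with baseline adjustment, against 0.93 for a t test on change and 0.77 to 0.98 for one on raw post-treatment scores. All these figures assume the pilot effect, equal visit correlations and a constant SD. The change is worth making because it is cheap and removes the ambiguity; the plan is not unworkable without it.

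**What to change.** Replace the repeated-measures ANOVA with a linear mixed model fitted by REML (MIXED in the SPSS package already named):

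- Outcomes: post-treatment and 8-week PSQI.
- Fixed effects: group, visit, group × visit, baseline PSQI and baseline × visit.
- Covariance: unstructured across the two visits.
- Data: all observed visits of all randomised patients.

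Name the end-of-treatment group contrast as the single primary test and the 8-week contrast as secondary. Label the t tests supportive. With complete data the end-of-treatment contrast matches the baseline-adjusted ANCOVA above.

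Patients with no post-baseline PSQI still add no outcome information. Add one sensitivity analysis that imputes real-arm dropouts from the sham arm.

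The cost is revised wording, slightly more analysis work and an explicit missing-at-random assumption for the primary model. Visits, recruitment and treatment do not change.

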Two recent neuroimaging studies used functional magnetic resonance imaging (fMRI) to analyze the resting state functional connection (RSFC) of NAc in ID patients and revealed abnormal RSFC between NAc and mPFC which suggest the brain related to the severity of insomnia [16, 17]. Shao et al. [16] proposed an abnormal NAC-mPFC circuit in ID. In addition, the hypothalamus, a central role in sleep-wake regulation, was recently used as the seed for functional connection by fMRI, and the results showed that the bilateral hypothalamus and bilateral mPFC resting state functional connection were enhanced in ID patients and were positively correlated with sleep quality [18]. Moreover, neuroimaging revealed reduced gray matter density [19, 20], abnormal regional homogeneity (ReHo) [21], amplitude of low-frequency fluctuations (ALFF) [22], and reduced activation of mPFC [23, 24]. These studies suggest that mPFC may play an important role in the pathophysiological mechanism of insomnia.

Therefore, we hypothesized that 1-Hz rTMS stimulation over mPFC would improve insomnia symptoms of ID patients by altering mPFC seed functional connectivity in the group receiving real mPFC-rTMS group compared with the sham mPFC-rTMS group.

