## Methods/design

### Objective

The study objectives are (1) to determine the efficacy of mPFC-rTMS for ID and (2) to elucidate the neural mechanisms for the effects of mPFC-rTMS on ID.

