## Discussion

Previous studies have shown that rTMS is effective in the treatment of insomnia, but no study selected targets based on neural network connectivity. We review the literature and find that mPFC may be one of the potential targets. Therefore, it is necessary to carry out further clinical trials to clarify the efficacy and possible neural mechanisms of mPFC-rTMS for ID patients. It is expected that this clinical trial will provide important data on the effect of rTMS and its possible neural mechanisms for ID.

We speculate that this effect may have relevance to the modulation mPFC-based functional connectivity. If our hypothesis is correct, functional connectivity maps of the sleep-related regions will be more modulated in the group receiving real mPFC-rTMS than in the sham mPFC-rTMS group. These results will provide insight into the potential mechanism of rTMS for ID.

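### The fMRI tests compare connectivity level by level and arm by arm, so they neither test the real-versus-sham difference in connectivity change nor link that change to PSQI change, as the mechanism hypothesis requires

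*Protocol article*

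**What the plan says.** All references are to the protocol article.

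- **Hypothesis (end of the Introduction).** Real stimulation, compared with sham, "would improve insomnia symptoms of ID patients by altering mPFC seed functional connectivity". No partner region is named.
- **Second objective (Objective).** "to elucidate the neural mechanisms for the effects of mPFC-rTMS on ID".
- **Background (Introduction).** Earlier imaging work "proposed an abnormal NAC-mPFC circuit in ID". Another cited study reports altered connectivity between hypothalamus and mPFC. Both support the choice of stimulation site.
- **Connectivity measure (Statistical analysis).** Pearson correlation "will be used to investigate the RSFC between bilateral mPFC and the whole-brain regions", followed by a Fisher *r*-to-*z* transform. The seed is fixed at the bilateral mPFC.
- **Between-arm test (Statistical analysis).** "mPFC-based functional connectivity pre-rTMS and post-rTMS between the real and sham mPFC-rTMS group will be compared using independent" *t* tests.
- **Within-arm test (Statistical analysis).** Paired *t* tests "will be used to compare pre-rTMS and post-rTMS mPFC-seed functional connectivity within each group".
- **Multiplicity (Statistical analysis).** P < 0.05 "after correcting for multiple comparisons using false discovery rate (FDR) correction".
- **Prediction (Discussion).** "functional connectivity maps of the sleep-related regions will be more modulated in the group receiving real mPFC-rTMS" than in the sham group. The regions are not listed.
- **Status (Sample size).** The fMRI part has no sample size calculation and is called exploratory.

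**The concern.** The hypothesis makes two claims: real stimulation changes mPFC-seed connectivity more than sham does, and this change goes with the improvement in sleep. The stated tests approach the first indirectly and do not reach the second.

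On the former, comparing arms separately before and after treatment, and each arm with itself, invites the familiar misreading in which a significant change under real stimulation and a non-significant one under sham is taken as a difference between them. On the latter, the only correlation in the plan is between time series within a scan. A PSQI effect and a connectivity effect could both appear and be unrelated across patients, and the analysis would look the same as if one carried the other.

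What is at stake is the second objective and the Abstract's expectation of strong evidence on mechanism. The PSQI efficacy result does not depend on any of this.

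**Working it through.** The plan gives no figure for the fMRI analysis, so there is none to reproduce. The sample size of 26 per group concerns PSQI and is not at issue here.

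**1. Claims against tests**

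| What the article claims | What would test it | What is stated |
|---|---|---|
| More modulation in real than sham | Between-arm difference in connectivity change, or group-by-time | Independent *t* tests pre and post; paired *t* tests within arm |
| Improvement occurs through altered connectivity | At least an association between connectivity change and PSQI change | None |

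The repeated-measures analysis of variance appears in the paragraph on clinical data. The fMRI paragraph lists its own tests and does not include it.

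**2. Why within-arm tests do not stand in for a between-arm test of change**

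Illustration with assumed values: 25 patients per arm, and mean changes of 0.5 SD (real) and 0.3 SD (sham), in units of the SD of change.

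- Real: t = 0.5 × √25 = 2.5, 24 df, P = 0.02.
- Sham: t = 0.3 × √25 = 1.5, 24 df, P = 0.15.
- Difference in change: t = (0.5 − 0.3) / √(2/25) = 0.2 / 0.283 = 0.71, 48 df, P = 0.48.

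The paired tests would suggest an effect of real stimulation only; the test of the difference would not.

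**3. What the link analysis could detect**

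Number with both scans: 60 × (1 − 0.15) = 51 after the stated 15% dropout, taken as 50. The documents give no expected correlation, so a range is assumed. Power at two-sided 0.05 is approximately Φ(atanh(r) × √(n − 3) − 1.96).

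- r = 0.3, n = 50: 0.310 × 6.856 − 1.96 = 0.16, power 56%.
- r = 0.4, n = 50: 0.424 × 6.856 − 1.96 = 0.94, power 83%.
- r = 0.5, n = 50: 0.549 × 6.856 − 1.96 = 1.81, power 96%.

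Adjusting for two covariates replaces n − 3 by n − 5 and barely matters: 55% at r = 0.3 and 96% at r = 0.5. These figures are for one prespecified connection; searching many lowers them.

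**4. Why the regression should adjust for group**

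If treatment shifts both measures, pooling the arms creates a correlation even when there is none within either arm. With equal arms and standardised group differences d₁ and d₂, the pooled r is (d₁/2)(d₂/2) / √[(1 + d₁²/4)(1 + d₂²/4)]. The pilot PSQI figures give d₁ = (4.43 − 1.30) / √[(3.60² + 2.58²)/2] = 3.13/3.13 = 1.00. With an assumed d₂ = 0.8 for connectivity, r = 0.5 × 0.4 / √(1.25 × 1.16) = 0.17. That is purely a group effect.

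**The case against.** Five points can be made for the plan.

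- **The seed analysis matches the hypothesis.** The hypothesis concerns mPFC-seed connectivity, and the plan measures exactly that. This stands. A reader might infer that the trial hypothesises a named circuit and then fails to test it. The documents do not support that: the accumbens and hypothalamus connections are background. Nor is it an unconstrained brain search, since the seed is fixed and FDR-corrected.
- **The post-treatment comparison is valid under randomisation.** This also stands. The arms are expected to be equal at baseline, so a post-treatment *t* test does estimate an effect of stimulation on connectivity. It would be too strong to say the plan has no between-arm test of that effect. But that test ignores each patient's own baseline and any chance imbalance, and the sentence does not say whether the post comparison, the pre comparison or a change score carries the conclusion.
- **The fMRI part is exploratory, and the Discussion speaks of speculation.** This lowers the weight of the point. It does not remove it, because the hypothesis, the second objective and the Abstract are worded more firmly.
- **An unseen analysis plan may add the link.** Possible. However, the article does spell out its fMRI tests, and those do not match its stated aim, so this is more than an omitted detail.
- **A regression cannot prove mechanism.** Correct. It would still be observational with respect to connectivity, which is why it belongs as exploratory with conclusions limited to association.

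One might also want the two background connections tested as confirmatory. The trial gives no basis for that: the fMRI part was not sized, and at an assumed d = 0.5 with 25 per arm, power at 0.025 is only 30%.

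**Conclusion.** The point holds as a mismatch between stated aim and stated analysis. The tests listed for fMRI do not compare connectivity change between arms and do not relate it to PSQI change, so the mechanistic part of the second objective cannot be answered by following them.

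It is moderate in weight: fMRI is secondary and labelled exploratory, and the PSQI result is unaffected. The conclusion rests on reading the between-arm sentence as separate pre and post comparisons. If a comparison of change scores was meant, the first half is a matter of wording and the second half remains. The power range for the link depends on assumed correlations of 0.3 to 0.5 and about 50 patients with both scans.

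**What to change.** In the fMRI part of the Statistical analysis section:

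1. State that the between-arm comparison is of baseline-to-post change in Fisher-z mPFC-seed connectivity (equivalently, the group-by-time term). Describe the within-arm paired tests as descriptive.
2. Name the mPFC connections with nucleus accumbens and hypothalamus, already used as rationale, as prespecified exploratory regions of interest. Keep the FDR-corrected whole-brain map alongside them.
3. Add an exploratory regression of PSQI change on connectivity change, adjusted for group and baseline PSQI.
4. Limit mechanism conclusions to association, and bring the hypothesis, second objective and Abstract into line with the exploratory label in the Sample size section.

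The alternative, if no link analysis is wanted, is to restate the second objective as describing connectivity differences between arms.

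Cost: wording, two atlas-defined regions and a little more analysis. PSQI and fMRI are already collected at the same visits, so no new scans are needed. To be credible, the change should be made before unblinding. The drawback is limited power for a modest link (about 56% at r = 0.3), so a null regression would not show that a link is absent.
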